### Ethics and dissemination

2.12

This trial was approved by Ethics Committee of Gansu Traditional Chinese Medicine Hospital.

Written inform consent will be obtained from all participants or their authorized agents. We will provide free drugs for patients in case and control group and strictly confidential the research data. The result of the trial will be presented on the website of the Chinese Clinical Trial Registry and published in open access journals.

## Results

3

The results of this trial will be published on the website of the China Clinical Trial Registration Center and in peer-reviewed journals or academic conferences.

## Discussion

4

The results showed that the Yuanhu Zhitong Drop Pill group was superior to the Western medicine group in terms of VAS scores, WOMAC scale assessment results, patient satisfaction, and gastrointestinal symptoms assessment scale (GSRS scale),^[22]^*P* < .05, adverse reactions. The number of cases was significantly less than that of the western medicine group. This shows that Yuanhu Zhitong drop pills can effectively relieve limb pain without side effects, can improve the quality of life of patients, and has a significant effect.

In recent years, with the continuous development of traditional Chinese medicine research, it has achieved significant results in the treatment of knee osteoarthritis. At the same time, with its unique advantages such as multiple targets for therapeutic effects and low toxic and side effects, it has obtained a large number of patients and doctors. There are still many deficiencies in the research of traditional Chinese medicine for knee osteoarthritis. There are some limitations with this study. First, the sample size of this study is small and it is a single-center randomized controlled study. Second, patients using VAS scores are too subjective. Third, a large number of clinical studies lack long-term efficacy. The safety of the drug need long time to observe.

Therefore, large-scale randomized double-blind controlled experiments should be carried out in future clinical research to strive for innovative and prospective related studies with rich center points and large sample sizes. In conclusion, we hope that the results of this study can provide new evidence for the treatment of early knee osteoarthritis pain with traditional Chinese medicine.

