## Introduction

1

Knee osteoarthritis (KOA) is a common chronic knee disease, with pain and limited function as the main causes.^[1,2]^ More than 9,000,000 people have been diagnosed with KOA through clinical and imaging methods in USA.^[3]^ In China, 19.4% of the elderly population more than 60 years of age suffer from KOA.^[4,5]^ According to the Bulletin of the World Health Organization, osteoarthritis is predicted to be the fourth leading cause of disability by 2020.^[6]^ Patients often have symptoms such as pain and dysactivity, which limits the mobility of patients, cause psychosocial problems such as low self-efficacy and depression, and decreases the quality of life.^[7,8]^ The current therapeutic for KOA were mainly aimed to reducing pain and improvement of joint mobility.^[9,10]^

According to the recent guidelines, knee replacement surgery was the only effective pain management approach for the end-stage KOA.^[11,12]^ For the non-surgical treatment of KOA, pharmacological, non-pharmacological and alternative treatments were widely applied in the clinical practice.^[13]^ Among them pharmacologic treatments were the mostly widely adopted. For example acetaminophen, topical treatment, nonsteroidal, anti-inflammatory drugs (NSAIDs), COX-2 inhibitors, opioids and intra-articular cartilage-protective agents.^[14]^ However, long time taking anti-inflammatory drugs was associated with serious adverse reactions, such as digestive and renal impairment.^[15]^ A number of patients had to stop taking drugs for the side effects. Most patients are unwilling to receive routine treatment due to side effects, contraindications, and unsatisfactory relief of symptoms.^[16]^ while not all the patients are the ideal surgical candidates, some patients afraid of operation. Therefore non-invasive, safe and effective treatment options are in great demand for those patients to improve symptoms.

Chinese medicine has been used to manage osteoarthropathy for thousands of years. Yuanhu Zhitong dropping pills were also applied for treat KOA. However its efficacy and security has not been reported in the literature. The purpose of this study is to assess the efficacy and security of Yuanhu Zhitong dropping pills for KOA, a large sample size and a reliable blind method will be used to draw a reliable conclusion.

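### The Discussion reports superiority and freedom from side effects although the trial's results are still to come, names no data source, and includes a scale the Methods do not list

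*Protocol article*

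**What the plan says.** The Discussion opens in the past tense: "The results showed that the Yuanhu Zhitong Drop Pill group was superior to the Western medicine group in terms of VAS scores". The same sentence adds WOMAC, patient satisfaction and the "gastrointestinal symptoms assessment scale (GSRS scale"), and attaches P < .05. On adverse reactions it continues: "The number of cases was significantly less than that of the western medicine group". It then concludes that "Yuanhu Zhitong drop pills can effectively relieve limb pain without side effects".

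Elsewhere the document treats the results as pending. Section 3 (Results) says only: "The results of this trial will be published on the website of the China Clinical Trial Registration Center". Section 2.12 says: "The result of the trial will be presented on the website of the Chinese Clinical Trial Registry". Section 2.1 gives July 2019 as the planned start of recruitment. The Discussion itself closes with a hope: "we hope that the results of this study can provide new evidence". On prior evidence for the drug in knee osteoarthritis, the Introduction says: "However its efficacy and security has not been reported in the literature".

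Section 2.8 lists the outcomes: knee pain on a 100 mm VAS (primary), then WOMAC and a patient satisfaction questionnaire (secondary). Section 2.9 plans recording of adverse events, with examples by body system. Section 2.11 calls a result significant if P < .01 and not significant if P > .01.

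**The concern.** The Introduction gives the study's purpose as assessing the efficacy and safety of the drug. The Discussion gives a favourable answer to both, against an active NSAID comparator, in a document that has no results to report. It supplies no means, standard deviations, event counts or numbers analysed, so nothing in the claim can be checked.

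Two things are at stake. A reader could cite the paragraph as trial evidence. And the status of the document as a prospective plan depends on where the sentences came from: if outcome data had been seen when it was written, readers need to know. The GSRS raises the same question on a smaller scale, because a later GSRS analysis could not be shown from this document to have been planned.

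**Working it through.** No figure in the superiority statement can be recomputed, because no data accompany it. The check compares the statements section by section.

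1. **Timing.** Sections 2.12 and 3 both put the results in the future. The Discussion's first sentence puts them in the past, and its last sentence puts them in the future again. For this trial's results, these cannot all be true.

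2. **Source.** The comparison (the drug against a Western medicine group) is of the same kind as this trial's, and three of the four measures (VAS, WOMAC, satisfaction) are this trial's outcomes. No pilot, earlier study or interim look is mentioned. The one reference mark in the sentence follows the name of the GSRS and most likely cites the scale. The source is therefore undisclosed.

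3. **Outcomes.** Claimed in the Discussion: VAS, WOMAC, satisfaction, GSRS. Planned in 2.8: VAS, WOMAC, satisfaction. Planned in 2.9: adverse-event recording, with digestive symptoms among the examples but no scale. Three of four match. In the text at hand the GSRS is named once, in the Discussion.

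4. **Threshold.** The planned rule in 2.11 is P < .01; the bound reported in the Discussion is P < .05. If P lies below .01, both statements call the result significant. If .01 < P < .05, the Discussion's statement is true but 2.11 says there is no significant difference. So P < .05 alone does not establish superiority under the document's own rule.

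5. **Safety.** The paragraph moves from fewer cases than the comparator to no side effects. The second does not follow from the first: a smaller number need not be zero. Section 2.9 lists possible adverse events for both drugs, and the Discussion's own limitations say that the drug's safety needs long observation, whereas treatment here lasts 4 weeks.

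**The case against.** The best defence is that the paragraph is misplaced text, perhaps carried over from another study. Its wording fits this: it speaks of a Western medicine group and limb pain, where the Methods speak of a control group and the knee, and it uses a scale the Methods lack. On that view the plan itself is sound, since no planned outcome, test, sample size or procedure depends on the paragraph, and the other faults are by-products of one error. The point about scope stands and limits the severity. It does not remove the contradiction, because the sentences are in the current document with no source given.

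Several stronger readings are tempting, and the document does not support them.

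- A reader might infer that the sentences cannot rest on any earlier data. The Introduction says only that nothing has been reported in the literature. That leaves room for an unpublished pilot, early data from this trial, or text from another study.
- A reader might infer the opposite, that the trial's outcomes were already known. That is possible, but nothing in the document shows it.
- A reader might infer that two decision thresholds compete. They do not: 2.11 is the only decision rule, and P < .05 in the Discussion is a reported bound that does not exclude P < .01.
- A reader might test the no-side-effects claim by asking what zero events in 30 patients could exclude. The paragraph never reports zero events, so such a calculation addresses a situation the document does not describe. The gap between fewer and none makes the point without it.

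**Conclusion.** The point holds as a contradiction within the document. Results for the trial's efficacy and safety question are stated as known in section 4 and as pending in 2.12 and 3, with no source named. Three consequences follow from the same paragraph: one of the four claimed measures is not in the plan, the reported bound of .05 does not by itself meet the planned .01, and the no-side-effects conclusion exceeds the evidence the paragraph itself describes.

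The size cannot be put as a number, because no data are given. The planned primary outcome, arms and sample size are unaffected. What is affected is what the trial may be said to have shown, and whether the outcome list can be trusted as prospective. The change should be made, although the design does not have to be altered.

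The conclusion assumes that the Discussion's adverse-reaction sentence, which is broken in the text, refers to cases of adverse reactions. It takes no position on where the sentences came from.

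**What to change.** First, state where the result sentences come from; deleting them without explanation could hide the more serious possibility.

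- If they come from a pilot or another study, say so and label them as such.
- If they come from data of this trial, disclose that outcome data had been seen.
- If no data exist, delete them.

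In every case remove the claim of no side effects.

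List the GSRS in 2.8.2 only if it was prespecified and is being collected from before the first dose. Otherwise remove it or label it post hoc. Keep the .01 in 2.11 as the only decision threshold.

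The cost is mainly wording in the Discussion, plus an entry in 2.8.2 if the GSRS qualifies. No extra visit is needed. A pre-dose GSRS cannot be recovered for patients already treated without one, so if recruitment has begun and the scale was not in use, it cannot be added as a prespecified outcome for them. The authors also give up any efficacy or safety claim until data are reported, and results between .01 and .05 may not be called significant.
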